### Data management and monitoring

We will collect the data by issuing questionnaires through WeChat in the form of “Questionnaire Star.” To enhance the accuracy of the data and maintain the quality of the data. All the data collected will be checked and collated by two dedicated data managers and then import into the Excel. These data will be kept confidentially until the end of the trial and will not be available to anyone except for the data administrator.

Our study will start in August 2021, and the specific study stages and procedures are shown in Fig. 1 and Table 1.

### Statistical analysis

The SPSS 26.0 software will be used for analysis. Measurement data will be expressed as *mean ± SD*, and enumeration data will be expressed as rate. Repeated measurement analysis of variance will be used for intra-group comparison of measurement data satisfying normal distribution, and SNK (Student-Newman-Keuls) method will be used for inter-group comparison; quantitative data will be tested by *χ*^*2*^. Nonparametric tests will be used for data that do not meet the normal distribution and equal variances. *P* ≤ 0.05 will be considered significant. PPS (per-protocol set) will be used in the current study, and only the data will be analyzed from the participants who will perform the whole process. For those who lack follow-up data, the data of the last observation carried forward.

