### Eligibility criteria of the participants

#### Diagnostic criteria

According to the Diagnostic and Statistical Manual of Mental Disorders (DSM-IV) prepared by the American Psychiatric Association, Diagnostic Criteria for Nicotine Dependence 292.0:Daily use of nicotine for at least 3 weeksMore than 4 of the symptoms that occur within 24 h after stopping or reducing smoking: dysthymia or depression, insomnia, irritability, anger, anxiety, difficulty concentrating, restlessness, slow heart rate, and increased appetite or weight gainClinically significant distress due to the above symptoms or functional deficits in social, occupational, and other important aspectsThese symptoms are not due to a physical condition and cannot be attributed to any other mental disorder

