### Randomization

A total of 96 eligible participants will be recruited from Chengguan, Xigu and Heping Districts, Lanzhou City, Gansu Province, by posters and the most popular and ubiquitous Chinese form of social media, WeChat.Sequence generation: A series of consecutive numbers (from 1 to 96) will be generated prior to the recruitment, and computer software (Microsoft Excel 2016) will be used to randomly assign each number to one of the four intervention groups (1: acupuncture combined with nicotine patch group (ACNP), 2: acupuncture combined with sham nicotine patch group (ACSNP), 3: sham acupuncture combined with nicotine patch group (SACNP), and 4: sham acupuncture combined with sham nicotine patch group (SACSNP)Allocation concealment mechanism: All will be performed in the double blind fashion. This randomization sequence will be inserted into sequentially numbered, opaque, sealed envelopes (to ensure allocation is concealed from assessors). These envelopes will be opened by the acupuncturist treating the patient

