#### Secondary outcome

Secondary measures included a modified Fagerstrom test for nicotine dependence (FTND) score, a Minnesota Nicotine Withdrawal Scale (MNWS), and modified Brief Questionnaire of Smoking Urge (QSU-Brief) score. The three scores will be used to reflect the severity of nicotine dependence, withdrawal symptoms, and smoking craving of the participants. The higher scores indicate, the more severe symptoms. Each patient will be asked a questionnaire prior to the treatment and at 1, 4, and 8 weeks after the treatment. Table 3 shows the specific observation points of each index during the study.

**Table 3 Tab3:** The measurement time points of various indicators

Indicators	Before start of treatment	Treatment period			End of the follow-up
		Week 1	Week 4	Week 8	
Abstinence rate				√	√
Relapse rate					√
Expiratory CO value	√			√	
FTND scores	√	√	√	√	
MNWS	√	√	√	√	
QSU-Brief scores	√	√	√	√	

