## Discussion

Smoking is not only a physical dependence, but also a psychological dependence, thus, smoking cessation requires more than a strong will [21]. This study can only be carried out when the participants have certain intentions to quit smoking. We will choose two methods of NRT and acupuncture for the combined intervention of smokers who are willing to quit. Acupuncture is a relatively common and effective method in traditional Chinese medicine, while NRT is the most commonly used of the internationally recognized interventions. This combination is rarely reported in the literature, and it is expected to achieve better outcomes. We know that smoking behavior falls under the category of “mental and behavioral disorders resulting from the use of psychoactive substances” [22]. Thus, the choice of control group will not be a single intervention, but a combination of a placebo treatment of another method, as well as a group of pure placebo group. Each group will receive two interventions designed to blind the participants and provide a psychological cue that will help improve the effect of the intervention and promote participant compliance with the regulations.

There is a paradigm shift towards patient-centered care and active involvement of participants and public in research design and active participation throughout the research process [23]. However, to ensure the implementation of blind method in the later stage of the experiment, this paradigm has not adopted in the design of this study, and the protocol designers will be all composed of trial researchers, without the participation of the public or participants.

There are several limitations in the current study. First, although we chose the double dummy to try to blind the study participants, we are unable to blind the physicians, which may lead to some bias. However, all the subjective indicators are collected through the network background, which will minimize these biases to some extent. Secondly, although we have performed the sample size calculation, the sample size is still small, and a large sample test will be needed in the future stage.

Our study will evaluate the efficacy and safety of different interventions for smoking cessation, providing some evidence for smokers to choose smoking cessation programs, as well as for future studies, and promote the development of acupuncture for smoking cessation. The results will be published within 6 months after the trial completed.

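### The repeated-measures ANOVA of FTND, MNWS and QSU-Brief is assigned to within-arm change only; the between-arm comparison (SNK) has no stated time point, baseline adjustment or group-by-time term

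*Protocol article*

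**What the plan says.** The Secondary outcome section of the protocol article names three scores: FTND, MNWS and QSU-Brief. On timing it says: "Each patient will be asked a questionnaire prior to the treatment and at 1, 4, and 8 weeks after the treatment". Table 3 places weeks 1, 4 and 8 within the treatment period, so each score has four occasions, one of them a baseline.

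The Statistical analysis section divides the work in one sentence. The first half reads "Repeated measurement analysis of variance will be used for intra-group comparison of measurement data satisfying normal distribution". The second half reads "SNK (Student-Newman-Keuls) method will be used for inter-group comparison". The fallback is "Nonparametric tests will be used for data that do not meet the normal distribution and equal variances", without saying whether that applies within arms, between arms or both. A threshold of P ≤ 0.05 "will be considered significant", with no distinction between within-arm and between-arm tests.

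For the SNK comparison the section states no visit, change score, baseline adjustment or group-by-time term.

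**The concern.** Repeated-measures ANOVA inside one arm tests whether that arm's mean differs across its own visits. Randomisation makes the arms comparable with each other; it does not make an arm comparable with its own past. The Discussion says of the population: "This study can only be carried out when the participants have certain intentions to quit smoking". It also expects that giving everyone two interventions will act as a helpful psychological cue. Scores may therefore improve in any arm, including the one given both shams, and a significant within-arm test is not evidence of a treatment effect.

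Two things are at stake. First, a report that follows the plan could show P values for change in each of four arms. A pattern of significance in some arms and not in others is easily taken for a treatment difference. Second, the baseline and repeated scores, which could sharpen the randomised comparison, are given no stated role in it.

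**Working it through.** The plan gives no figure for this analysis, so there is none to reproduce. The check asks how often separate within-arm tests disagree when the arms do not differ.

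**Inputs from the protocol article**
- Four arms of 24, and a 30% loss allowance (Sample size calculation). 24 × 0.7 = 16.8, taken as 17 completers per arm; 24 is full retention.
- Four occasions (Secondary outcome, Table 3).
- Threshold 0.05 for each test (Statistical analysis), taken as two-sided.

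**Assumptions, because the document gives no values**
- The same true change in every arm, d = 0.3 to 0.8 SD of the change.
- A paired t-test as an approximation to the planned ANOVA over four visits.

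**Formulas**
- w = probability that one arm is significant = power of a two-sided 5% paired t-test with n − 1 degrees of freedom and noncentrality d√n.
- Two given arms disagree: 2w(1 − w).
- Some but not all of four arms significant: 1 − w⁴ − (1 − w)⁴.

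**Example: d = 0.5, n = 17**
- Noncentrality 0.5 × √17 = 2.062; critical t on 16 degrees of freedom 2.120; w = 0.491.
- Two arms disagree: 2 × 0.491 × 0.509 = 0.500.
- Mixed pattern: 1 − 0.491⁴ − 0.509⁴ = 1 − 0.058 − 0.067 = 0.875 (0.8748 before rounding, that is 87%).

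**Range**

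| d | w, n = 17 | Mixed pattern, n = 17 | Mixed pattern, n = 24 |
|---|---|---|---|
| 0.3 | 0.214 | 62% | 74% |
| 0.4 | 0.341 | 80% | 87% |
| 0.5 | 0.491 | 87% | 81% |
| 0.6 | 0.642 | 81% | 58% |
| 0.8 | 0.872 | 42% | 14% |

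**Check with the ANOVA itself.** A simulation (3,000 runs per setting) used four arms and four visits. All arms had the same linear decline of 0.5 to 1.0 SD of the score from baseline to week 8, and the within-person correlation was 0.3 to 0.7, all assumed. These SDs are of the score, not of the change, so the scale differs from the table.
- At a 0.5 SD decline, the mixed pattern occurred in 74% to 85% of runs with 17 per arm and in 62% to 86% with 24.
- At 0.8 and 1.0 SD the mixed pattern becomes less frequent (1% to 80% with 17 per arm), because most or all arms turn significant.
- Over all settings, the sham/sham arm was significant in 30% to 99.8% of runs with 17 per arm and in 40% to 100% with 24.
- A single group-by-time test across the arms rejected in 4.3% to 6.1% of runs, as it should when the arms do not differ.

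**The case against.** The strongest reply is that the same sentence gives the scores a between-arm analysis. That stands. SNK on week-8 values or on changes from baseline would be a valid randomised contrast, and on changes it would compare change between arms directly. A reader might infer from the word intra-group that the plan has no test of treatment differences at all; the second half of the sentence rules that out. Nor does the text say that SNK is run visit by visit.

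SNK usually follows an ANOVA with a group factor, so the sentence could also be read as one joint analysis. The wording does not favour this, since it ties the ANOVA to within-group use. Even on that reading, a comparison of arm averages over visits is not a test of differing change. A fuller analysis plan may supply details, but the assignment of the longitudinal model to within-arm comparison is stated here, not left open.

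It is also fair that the mixed-pattern probabilities describe a misreading. They do harm only if someone infers efficacy by comparing within-arm P values, which the plan does not propose. It does not exclude it either, because the within-arm tests are not marked as descriptive.

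Two further inferences are tempting and unsupported:
- Regression to the mean in MNWS. The Diagnostic criteria concern "the symptoms that occur within 24 h after stopping or reducing smoking". They set no threshold on the MNWS score taken before treatment, so no size can be given for such an effect here.
- Confounding of visit with schedule in the patch arms alone. The step from three to two acupuncture sessions a week applies to all participants, and Table 2 is introduced for nicotine and sham patches alike.

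Lastly, a mixed model is not the only sound choice; a baseline-adjusted comparison at week 8 would also answer the question.

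**Conclusion.** The concern holds in a limited form. The one longitudinal method in the plan is assigned to a question that cannot compare treatments, and the stated between-arm method has no specified time point, change score, baseline adjustment or group-by-time term.

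With no difference between arms, separate within-arm tests give a mixed pattern with probability 42% to 87% at 17 completers per arm and 14% to 87% at 24, so full retention does not remove the problem. These figures rest on assumed changes of 0.3 to 0.8 SD, equal in all arms, and on a paired test standing in for the ANOVA. The simulation with the ANOVA itself agrees for moderate declines and shows fewer mixed patterns when the common decline is large.

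The point is limited to the three secondary scores. Abstinence and relapse are rates and are not affected. The change is worth making because it is cheap, not because the between-arm test as stated is invalid.

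**What to change.** In the Statistical analysis section, replace the split between within-arm ANOVA and SNK for FTND, MNWS and QSU-Brief with wording such as:

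*Each score will be analysed in one repeated-measures or linear mixed model across all four arms, with arm, visit and arm-by-visit terms and with the baseline score accounted for. The reported effect is the between-arm difference at week 8 with its 95% CI. Within-arm changes will be shown descriptively, without P values, and no efficacy claim will rest on them.*

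The cost is a rewording. No further data or participants are needed, and the model runs in the software already named. The downside is that the within-arm P values are lost.

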### Sample size calculation

We will use the calculation formula of sample size of enumeration data in a completely random design, as describe previously. The PASS software will be used for calculation. The formula is listed as follow:$$N=\frac{\Big[{Z}_{\alpha}\sqrt{2p\left(1-p\right)}+{Z}_{\beta }{\sqrt{p_1\left(1-{p}_1\right)+{p}_2\left(1-{p}_2\right)\Big]}}^2}{{\left({p}_1-{p}_2\right)}^2}$$

*α* = 0.05 will be set up as the level of test, and the test power is 90%. The withdrawal rates of acupuncture (*p*_1_) and placebo (*p*_2_) will be 56% [18] and 9.1% [19], respectively; *p* is the mean of *p*_1_ and *p*_2_. The PASS 26.0 software will be used to calculate that the sample size required for each group for ≥18 cases. Considering 30% loss to follow-up rate, the sample size per group will be 24 cases. Consequently, the total number of the participants will be 96, based on 24 case per group in the four groups.

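### The only parametric between-group method named for CO and the three scores is SNK, which uses no baseline and does not hold 5% familywise error; repeated-measures ANOVA is kept for within-group change, and the chi-square wording is wrong

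*Protocol article*

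**What the plan says.** The protocol article's Statistical analysis section fixes three things.

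- Within groups: "Repeated measurement analysis of variance will be used for intra-group comparison of measurement data satisfying normal distribution".
- Between groups, and for a further class of data: "SNK (Student-Newman-Keuls) method will be used for inter-group comparison; quantitative data will be tested by" chi-square.
- Where normality and equal variances fail, nonparametric tests that it does not name. The significance threshold is P ≤ 0.05.

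The section mentions no baseline covariate, change score, group-by-time term or overall between-group test.

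The Primary outcome section lists three main outcomes: abstinence and relapse, which are rates, and expiratory CO, which is continuous. Table 3 schedules CO before treatment and at week 8. It schedules FTND, MNWS and QSU-Brief before treatment and at weeks 1, 4 and 8. The Secondary outcome section agrees on the pre-treatment value of the scores: "Each patient will be asked a questionnaire prior to the treatment".

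**The concern.** The trial randomises to four arms in order to compare them. Yet the one method in the plan that can handle repeated measurements is reserved for change inside an arm. For CO, with one value before treatment and one at week 8, that is simply a before-after test. Participants are smokers who want to quit, so improvement could appear in any arm, including double sham, and a significant within-arm p-value could be misread as efficacy.

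The between-arm question is left to SNK. SNK compares group means, as stated without the baseline values that the trial collects. It also does not control familywise error at 5% in every pattern of true means. Arms of 24 are small, and the Discussion says so, which makes lost precision and extra false positives matter more.

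Finally, chi-square is attached to the wrong type of data, so two primary outcomes have no correctly named test on a literal reading.

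**Working it through.** **1. The plan's own figure.** Inputs from Sample size calculation: alpha 0.05, power 90%, and rates that "will be 56% [18] and 9.1% [19], respectively". The mean rate is p = (0.56 + 0.091)/2 = 0.3255. With the printed formula and a two-sided test:

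- 1.960 × √(2 × 0.3255 × 0.6745) = 1.299
- 1.282 × √(0.56 × 0.44 + 0.091 × 0.909) = 0.735
- (1.299 + 0.735)² / 0.469² ≈ 18.8, so 19 per group; one-sided it is 16

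The plan states "sample size required for each group for ≥18 cases", which is within one patient of the two-sided result. Then 18 × 1.3 = 23.4 gives the stated 24, and 4 × 24 = 96. This calculation covers one binary comparison. It says nothing about power for CO or the scores, so the choice of test for those outcomes is not protected by it.

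**2. Data collected against method named.**

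| Outcome | Collected (Table 3) | Between-group method named |
|---|---|---|
| Abstinence | week 8, end of follow-up | none on a literal reading; chi-square if the wording is a slip |
| Relapse | end of follow-up | as above |
| CO | baseline, week 8 | SNK, no baseline |
| FTND, MNWS, QSU-Brief | baseline, weeks 1, 4, 8 | SNK, no baseline or group-by-time term |

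**3. SNK error rate.** Suppose only one treatment works, for example the patch. The two patch arms then share one mean and the two sham-patch arms share another. Once the pairs are well separated, SNK tests each equal pair at 5%:

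1 − 0.95² = 0.0975

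A simulation of SNK with four groups (40,000 runs per setting) gives:

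| True pattern | n per arm | Familywise error |
|---|---|---|
| all four equal | 24 | 5.2% |
| two pairs, 0.8 SD apart | 24 | 9.2% |
| two pairs, 1.2 SD apart | 24 | 9.7% |
| two pairs, 0.8 SD apart | 18 | 8.8% |
| two pairs, 1.2 SD apart | 18 | 9.5% |

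**4. Value of the baseline.** With baseline-outcome correlation r, ANCOVA leaves a residual variance of 1 − r². The equivalent gain in sample size is 1/(1 − r²). The documents give no r, SD or effect size for CO or the scores. The table assumes a standardised difference of 0.8, two-sided alpha 0.05, one pairwise contrast and the normal approximation: power = Φ(0.8 × √(n/2) / √(1 − r²) − 1.96).

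| r (assumed) | Variance cut | Sample-size equivalent | Power, n = 24 | Power, n = 18 |
|---|---|---|---|---|
| 0 | 0% | 1.0 | 79% | 67% |
| 0.3 | 9% | 1.1 | 83% | 71% |
| 0.5 | 25% | 1.3 | 89% | 79% |
| 0.7 | 49% | 2.0 | 97% | 92% |

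**5. What happens if SNK is only removed.** Four arms give 4 × 3/2 = 6 pairwise contrasts. Tested without adjustment, they carry about 20% familywise error when all arms are equal, against SNK's 5%, and the same 9.75% in the two-pairs pattern. SNK therefore has to be replaced, not just deleted.

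**The case against.** Several objections have force.

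- **Chi-square.** A reader might infer that CO would be tested by chi-square. The text does not support that. The section divides data into measurement data (mean and SD) and enumeration data (rates), and gives measurement data its own methods before it reaches chi-square. What remains can only be the rates. The word is wrong and needs correcting, but it does not show a wrong test for CO.
- **Baseline.** An unadjusted comparison of randomised groups is valid, and a covariate could be named in a fuller document that is not shown. So the lack of adjustment is a loss of precision, not a bias, and its size depends on an assumed correlation. Nor is the unadjusted comparison the least efficient choice: a change score has variance factor 2(1 − r), which is worse whenever r is below 0.5.
- **SNK.** The excess error is specific to a pattern of means; with all arms equal SNK is close to nominal. The complaint about ignored repeated measurements does not apply to CO, which has one post-baseline value. For the scores, the text does not say whether SNK is run at each visit or as a post hoc step of a larger model. Where normality and equal variances fail, SNK would give way to an unnamed nonparametric test, though no baseline is mentioned there either.
- **Within-group tests.** A reader might infer that every arm is bound to show improvement. The documents do not establish that; it is only plausible in people who want to quit.
- **Scope.** The outcome used to size the trial is binary, and the baseline, SNK and within-group points do not touch it.

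What survives does not depend on silence: the restriction of repeated-measures ANOVA to within-group change, SNK as the named between-group method, and the chi-square wording are all affirmative statements.

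**Conclusion.** The point holds at moderate weight and should be fixed before analysis. As written, the randomised comparison for one primary outcome (CO) and all three secondary scores rests on a procedure whose familywise error reaches about 9.75% in a realistic pattern for this design, namely that only one treatment works. That procedure also leaves the scheduled baseline values unused. Adjusting for them would be worth about 1.1, 1.3 or 2.0 times the sample size at assumed correlations of 0.3, 0.5 or 0.7, and nothing at zero. The power figures rest further on an assumed standardised difference of 0.8. The chi-square sentence is most likely a one-word slip, but it concerns two primary outcomes and must be corrected under either reading.

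**What to change.** Amend the Statistical analysis section as follows.

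- **Abstinence and relapse:** change quantitative to enumeration data. State that both rates are compared between the randomised groups by chi-square, or Fisher's exact test where cells are small (or logistic regression), with risk differences and 95% confidence intervals.
- **CO at week 8:** ANCOVA on baseline CO, log-transformed if skewed.
- **FTND, MNWS and QSU-Brief:** a mixed model for weeks 1, 4 and 8 with group, time, group-by-time and baseline score. The between-group difference at week 8 is the estimate.
- **Multiplicity across arms:** replace SNK with a procedure that controls familywise error in every configuration, such as Tukey for all pairs or Holm on a short prespecified list of contrasts.
- **Within-group tests:** keep as descriptive only.

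The cost is slightly wider critical values than SNK gives and a little more analysis work. The visits, measurements and software (SPSS 26.0) stay as planned.

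### Rank tests are the only remedy named for unequal variances, which they do not correct, so for CO and the three questionnaire scores the 5% error rate is not assured (minor)

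*Protocol article*

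**What the plan says.** All of this is in the Statistical analysis section of the protocol article.

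- Summary: "Measurement data will be expressed as" mean ± SD, with no separate summary for data analysed by ranks.
- Within groups: "Repeated measurement analysis of variance will be used for intra-group comparison of measurement data satisfying normal distribution".
- Between groups: "SNK (Student-Newman-Keuls) method will be used for inter-group comparison".
- Fallback: "Nonparametric tests will be used for data that do not meet the normal distribution and equal variances".
- Level: P ≤ "0.05 will be considered significant".
- Analysis set: participants who complete the whole process.

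The outcomes touched are expiratory CO, one of three primary outcomes, and the secondary scores FTND, MNWS and QSU-Brief. The article gives no SDs for them and no expected number of completers by arm.

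**The concern.** A Kruskal-Wallis or Mann-Whitney test compares locations only if the distributions share the same spread and shape. Sending data to ranks because their variances differ keeps the problem that triggered the switch. The wording can also be read as requiring both assumptions to fail. On that reading, normal data with unequal variances stay with the mean-based methods. Either way, no method that allows for unequal variances is named.

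Two consequences follow. The false-positive rate depends on which arm happens to be more variable, not on the stated 5%. And a mean difference in a results table may stand beside a P value that tests something other than equal means.

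**Working it through.** **Arm sizes.** The sample size gives the context for how large the analysed arms will be. The planning rates "will be 56% [18] and 9.1% [19], respectively" go into the printed formula, with p = (0.56 + 0.091)/2 = 0.3255, two-sided 5% and 90% power:

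N = [1.960 × √(2 × 0.3255 × 0.6745) + 1.282 × √(0.56 × 0.44 + 0.091 × 0.909)]² / 0.469² = 18.8

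The article states "the sample size required for each group for ≥18 cases", which agrees to within one participant. Then 18 × 1.3 = 23.4, which rounds up to the stated 24. With 30% loss, 24 × 0.7 = 16.8, or about 17 completers per arm if loss is even.

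**Simulation with normal data and equal means, nominal 5%, 40,000 runs per row.** The SDs and completer counts are assumptions: SD ratios of 1 to 3, and arms from equal to 24/24/12/12. The two-stage rule stands in for the plan: Levene P ≤ 0.05 leads to Kruskal-Wallis (KW), otherwise to ANOVA. The article names neither the pre-test nor the rank test, and SNK itself was not simulated.

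| Arm sizes | SDs | ANOVA | KW | Two-stage | Welch |
|---|---|---|---|---|---|
| 24/22/18/14 | 1/1/1/1 | 5.0% | 4.5% | 4.9% | 4.9% |
| 24/24/24/24 | 1/1/1/2 | 6.7% | 5.5% | 5.5% | 5.0% |
| 24/22/18/14 | 1/1/1/2 | 10.2% | 6.6% | 7.3% | 5.2% |
| 24/24/12/12 | 1/1/2/2 | 13.3% | 8.5% | 9.0% | 5.2% |
| 24/24/12/12 | 1/1/3/3 | 17.2% | 10.5% | 10.5% | 5.0% |
| 24/22/18/14 | 2/1.5/1/1 | 4.1% | 4.1% | 4.0% | 5.0% |
| 24/24/12/12 | 2/2/1/1 | 3.1% | 3.4% | 3.2% | 5.2% |

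- Row 1: unequal sizes with equal SDs do no harm, even with a data-driven choice.
- Rows 3 to 5: the error rises when the smaller arms are the more variable.
- Rows 6 and 7: the error falls when the larger arms are the more variable.
- Welch ANOVA stays near 5% throughout.

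A separate run with arms of 22/18/17/11 and SD 2 in the smallest gave 6.9% for Kruskal-Wallis and 8.1% for the two-stage rule. The pre-test missed the unequal variances in about a third of runs and kept ANOVA, whose error was 11.3%. With SD 2 in the largest arm instead, the figures were 4.5% and 4.2%.

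**Random loss.** Kruskal-Wallis with 30% random loss, 12,000 runs:

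| SDs | From 24 per arm | From unblocked allocation |
|---|---|---|
| 1/1/1/1.73 | 5.1% | 5.3% |
| 1/1/1.73/1.73 | 4.8% | 5.1% |
| 1/1/1/2 | 5.4% | 5.2% |
| 1/1/2/2 | 5.8% | 5.9% |

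**Skewed data.** With equal means and one arm at 1.73 times the SD of the others, Kruskal-Wallis rejected in 13% of runs and Welch in 6%. A centred exponential shape with 17 or 18 per arm reproduces this. The rank test is detecting a real difference in distribution, but the means in the table would be equal. Welch is approximate under skew, not exact.

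**The case against.** The case for leaving the text alone is substantial, and most of it stands.

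- **Unequal arms by themselves.** A reader might infer that arms ending unequal in size push the error above 5%. The table does not support that: size matters only in combination with unequal SDs, and the direction can go either way.
- **Chance imbalance.** Random loss and random allocation are unrelated to variance, so favourable and adverse pairings largely average out. Two arms at 12 or fewer with two at 22 or more occurred in about 0.3% of unblocked runs, and never from 24 per arm. Starting from 24, it takes about 50% loss in the variable arms and 8% in the others. Nothing in the article suggests this.
- **The planning rates.** It is tempting to argue that 56% against 9.1% quitting makes unequal CO variance expected: 0.56 × 0.44 = 0.246 against 0.091 × 0.909 = 0.083, a ratio of 2.98 and an SD ratio of 1.73. But in such a two-level model unequal quit rates also mean unequal mean CO, so this is not a false-positive scenario. It gives no information about the three scores.
- **Choice by result.** A reader might infer that analysts who know the results pick the test. The article describes an assumption check and restricts data access until the trial ends. Nor does it say that the choice is repeated for each outcome and visit.
- **Ranks against ANOVA.** In the same adverse setting Kruskal-Wallis inflates less than ANOVA (6.6% against 10.2%), so the fallback is a partial improvement.
- **Level of detail.** Which nonparametric test to use may properly be left to an analysis plan.

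What survives is narrower. The article does fix a remedy for unequal variances, and that remedy does not do what it is there for. It also fixes mean ± SD as the summary whichever test supplies the P value.

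**Conclusion.** The point holds as a minor one. For expiratory CO, FTND, MNWS and QSU-Brief the stated rule does not hold the error at 5%. With normal data it is about 7-9% when a clearly smaller arm is the more variable (10.5% in the most extreme setting tried), about 4% when the larger arm is, and mostly within one point of 5% when 30% are lost at random. With skewed data of unequal spread, a rank P value can be significant while the reported means are equal.

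Abstinence and relapse, the other two primary outcomes, are not affected. The figures rest on assumed SD ratios and completer counts, and on Levene with Kruskal-Wallis or ANOVA standing in for tests the article does not name.

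**What to change.** In Statistical analysis, remove the test-dependent switch and name one method per type of outcome, with a summary that matches it.

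- **FTND, MNWS, QSU-Brief:** Welch ANOVA with Games-Howell pairwise comparisons, or a model with arm-specific variances. Report mean differences with confidence intervals, whatever any normality or variance check shows.
- **Week-8 CO:** either the same approach on a suitable scale chosen in advance, or a rank method valid under unequal spread, such as Brunner-Munzel, reported with medians and the relative effect. A location-shift interval should not accompany it, because that interval assumes equal spread and shape.

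The cost is about two sentences and a slight loss of power if variances turn out equal.
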